Against this background and based on our previous studies [24–30], we propose that PMC might play a key role beyond M1. This can be attributed to several reasons. First, homologous regions of bilateral hemispheres are connected through the corpus callosum, and the connections between bilateral PMC form the largest proportion of white matter fibers of the corpus callosum, rather than between bilateral M1 [26]. This provides the structural basis for the existence of IHI in PMC as it is in M1. Thus, the interaction between bilateral PMC in stroke recovery is worth more attention. Second, PMC is composed of the dorsal part (PMd) and the ventral part (PMv). Previous studies revealed that PMd was involved in the coordination and control of the complex movements of hands [27]. Uncrossed corticospinal ventral tracts originating ipsilateral from PMd (approximately 10–20% of CST) were also found in animal studies [28]. Moreover, PMd is associated with the reticulospinal tract and the red nucleus spinal tract emanating from the brain stem, mainly inculcating the ipsilateral proximal limb [29]. This implies that cPMd may play a compensatory role in promoting motor functional recovery through the ipsilateral inculcating pathway. Third, we have previously conducted a resting-state fMRI study in chronic stroke patients, and found that the betweenness centrality (BC) of cPMd in the stroke group was significantly lower than that in the healthy group. In addition, the BC value of cPMd was significantly positively correlated with the score of the upper limb motor function on the ipsilateral side. These results suggest that the more compensatory effects cPMd provide, the better the motor prognosis for severe stroke patients [30]. Based on the above three points, we hypothesized that cPMd may play a role as a potential target brain area for promoting brain reorganization in rTMS therapy.

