### Conventional rehabilitation intervention and rTMS intervention

In addition to the routine pharmacotherapy, the three groups of patients will undergo 40 min of conventional rehabilitation, including physical therapy of upper limb function (PT) and daily living ability training (OT), once each day, 5 days a week, for a total of 3 weeks. Moreover, all stroke patients will receive the same dose of other routine rehabilitation treatments such as biofeedback electrical stimulation, acupuncture, and massage for 3 weeks.

For rTMS intervention, ① patients in the cM1-LF group will be treated as follows: 100 sessions of 1 Hz rTMS at 90% resting motor threshold (RMT) to cM1 (at the optimal stimulus point with the largest and most consistent MEP), 10 pulses per session with a 2-s interval between sessions, totaling 1000 pulses (20 min); ② patients in the cPMd-HF group will be treated as follows: 20 sessions of 5 Hz rTMS at 90% RMT to cPMd (2 cm in front and 1 cm in the inner side of the optimal stimulus point of M1), 50 pulses per session with a 50-s interval between sessions, totaling 1000 pulses (20 min) (Fig. 2); and ③ patients in the CON group will be treated with the same parameters as cM1-LF group (including location, stimulation frequency, and time), however, the coil will be placed perpendicular to the surface of the skull to emit the same stimulating sound as the cM1-LF group but without effective stimulation. All patients in the three groups will receive rTMS intervention once a day for 5 days a week, for 3 weeks.

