#### DTI

The bilateral posterior limb of internal capsule (PLIC), bilateral cerebral peduncle, and corpus callosum of each patient will be delineated manually by two radiologists. For each patient, the common part of the results recorded by the two radiologists will be adopted as the regions of interest (ROIs). The mean fractional anisotropy (FA) will be calculated with all the ROIs for each hemisphere. Notably, FA asymmetery index (FA AI) is defined by the following formula:

$$FA\ AI=\frac{\left({FA}_c-{FA}_a\right)}{\left({FA}_c+{FA}_a\right)}$$where FAc is the FA of the contralesional hemisphere and FAa is the FA of the affected hemisphere. FA AI can be used to quantitatively evaluate the structural integrity of CST and corpus callosum.

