#### Group-level analysis

All statistical analyses will be performed using SPSS software (SPSS 25.0, SPSS Inc., Chicago, Illinois). The intention-to-treat principle will be used for the analysis of functional and electrophysiological data. One-way analysis of variance (ANOVA) will be used to compare the demographic characteristics and baseline assessment (T0) of all outcomes among groups. To compare the treatment effects of different rTMS protocol, a two-way mixed design ANOVA with between-subject factor “Group” and within-subject factor “Time” will be performed for the clinical and electrophysiological changes. Moreover, Bonferroni correction will be employed for post hoc multiple comparisons. *P* < 0.05 will be considered statistically significant for all analyses.

For rs-fMRI and DTI data, a two-way mixed design ANOVA will be performed, with between-subject factor “Group” and within-subject factor “Time” on the data generated in the data processing step, including Eg, El, network betweenness, clustering coefficient, and FA AI. For tb-fMRI data, a whole brain paired T-test will be performed between the task state blocks and baseline blocks in the FC group, and the voxels whose t value is higher than the threshold will be regarded as the activated brain region. For cM1-LF, cPMd-HF, and CON groups, a two-way mixed design ANOVA, with between-subject factor “Group” and within-subject factor “Time” will be performed within the former activated brain region. The most significant point of “Group” × “Time” effect in the activated brain region will be used as the center to construct spherical balls with a radius of 6 mm, and the spherical balls will be regarded as the ROIs. Finally, to obtain the effective connectivity of each patient at different time points, the average time series of all voxels in each ROI will be subjected to dynamic causal model (DCM) analysis.

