In addition to potential clinical influence, the study will elucidate the underlying mechanism of brain plasticity though longitudinal analysis of multimodal fMRI data scanned before and after the intervention, and during the follow up. It is worth noting that rest-state fMRI will provide information about the changes of brain networks, task-based fMRI will display the brain activation model of specific task instantly, and DTI will provide insights into the remodeling of motor pathway. Collectively, the results will help us to further understand the neural effects of different protocols of rTMS therapy in stroke rehabilitation. Furthermore, the joint analysis of neuroimaging data and functional changes will indicate the cut-off that separates mildly from severely affected patients, ultimately guiding application of tailored stimulation parameters for rTMS (i.e. low-frequency rTMS on cM1 or high-frequency rTMS on cPMd). In conclusion, this study will provide a theoretical basis for clarifying the bimodal balance-recovery model of stroke, provide biological markers for predicting the functional prognosis in chronic stroke patients after rTMS therapy, and provide a strategy for individualized rTMS treatment for stroke in future studies and clinical practice.

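### FA AI, the only DTI quantity named for the Group × Time analysis, cannot show which hemisphere changed, so any change over T0 to T2 is ambiguous

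*Protocol article*

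**What the plan says.** All statements are in the protocol article.

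- **DTI section.** Two radiologists outline the posterior limb of the internal capsule and the cerebral peduncle on both sides, and the corpus callosum. Then "The mean fractional anisotropy (FA) will be calculated with all the ROIs for each hemisphere". The two hemispheric means are combined as FA AI = (FAc − FAa)/(FAc + FAa), "where FAc is the FA of the contralesional hemisphere and FAa is the FA of the affected hemisphere". Its purpose is given as "FA AI can be used to quantitatively evaluate the structural integrity of CST and corpus callosum".
- **Group-level analysis section.** The rs-fMRI and DTI data go into a two-way mixed ANOVA (Group, Time), with the quantities listed as "including Eg, El, network betweenness, clustering coefficient, and FA AI". The first four are the network measures defined in the Rs-fMRI section, so FA AI is the only DTI quantity named.
- **rTMS intervention section.** One active arm receives "100 sessions of 1 Hz rTMS at 90% resting motor threshold (RMT) to cM1", the other "20 sessions of 5 Hz rTMS at 90% RMT to cPMd". Both targets are contralesional.
- **Background.** On the ipsilaterally projecting pathways of the dorsal premotor cortex: "This implies that cPMd may play a compensatory role in promoting motor functional recovery through the ipsilateral inculcating pathway".
- **Discussion.** The purpose of the longitudinal imaging includes that "DTI will provide insights into the remodeling of motor pathway".

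**The concern.** An asymmetry index tracks the integrity of the affected side only while the other side is a stable reference. At T0 that is reasonable, because neither hemisphere has yet been treated in the trial and the index describes how unequal the two sides are. From T0 to T2 it is less safe. The reference side is the one both active regimens act on, and the one the Background expects to compensate.

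A difference between groups in FA AI change could then come from the contralesional side, the affected side or both, and the index alone would not say which. The DTI analysis is meant to inform on motor pathway remodelling, and for that the side of the change is the substance of the question. The Correlation analysis section also relates MRI parameters to clinical scores in the two active groups, so an ambiguous FA AI could carry over into those results. The clinical comparisons are not affected.

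**Working it through.** **Inputs.** The formula and the meaning of FAc and FAa come from the DTI section. The protocol states no FA value and no expected change, so there is no figure to reproduce. Assumed for illustration: FAc = 0.60; FAa = 0.55, 0.45 or 0.35; a 5% change.

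**Step 1: algebra, with no assumed values.** Put r = FAc/FAa. Dividing numerator and denominator by FAa gives

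FA AI = (r − 1)/(r + 1).

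The index depends on the two FA values only through r. Its partial derivatives are

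- with respect to FAc: 2·FAa/(FAc + FAa)², always positive;
- with respect to FAa: −2·FAc/(FAc + FAa)², always negative.

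Three results follow:

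- FAc × 1.05 and FAa ÷ 1.05 both multiply r by 1.05, so they give the same index.
- The same proportional change on both sides leaves r, and so the index, unchanged.
- If both sides gain but FAc gains proportionally more, the index rises.

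**Step 2: illustration with the assumed values.**

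| FAc / FAa | Baseline | FAc × 1.05 | FAa ÷ 1.05 | Both × 1.05 | FAc × 1.05, FAa × 1.02 |
|---|---|---|---|---|---|
| 0.60 / 0.55 | 0.0435 | 0.0678 | 0.0678 | 0.0435 | 0.0579 |
| 0.60 / 0.45 | 0.1429 | 0.1667 | 0.1667 | 0.1429 | 0.1570 |
| 0.60 / 0.35 | 0.2632 | 0.2857 | 0.2857 | 0.2632 | 0.2766 |

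Middle row in full:

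- baseline: 0.15/1.05 = 0.1429;
- FAc up 5%: (0.63 − 0.45)/(0.63 + 0.45) = 0.18/1.08 = 0.1667;
- FAa down to 0.45/1.05 = 0.4286: 0.1714/1.0286 = 0.1667;
- FAc up 5% and FAa up 2%: (0.63 − 0.459)/(0.63 + 0.459) = 0.171/1.089 = 0.1570.

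**Step 3: size.** The absolute shift for a 5% change on one side is 0.0243, 0.0238 and 0.0225 in the three rows. Relative to baseline it is 56% (0.0243/0.0435), 17% (0.0238/0.1429) and 9% (0.0225/0.2632). The relative figures vary mainly because the baseline index is small when the sides are nearly equal, so the absolute shift is the steadier description.

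**Step 4: what the components would show.** Analysed separately, the two cases that share one index value come apart. A contralesional gain appears as FAc +5% with FAa unchanged. An affected-side loss appears as FAa −4.8% (1/1.05 − 1) with FAc unchanged.

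**The case against.** The case on the other side has several parts.

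- **The list may not be closed.** The Group-level analysis section applies the ANOVA to data from the processing step and introduces its list with the word including. Hemispheric mean FA is produced in that step, so it may fall within scope, and the full protocol or SAP may show the components. This stands in part: FA AI is the only DTI quantity named, which is not proof that it is the only one that will be analysed.
- **No misreporting is stated.** A reader might infer that a contralesional gain under high-frequency cPMd stimulation will be reported as loss of corticospinal tract integrity. The protocol does not support that. It calls FA AI a measure of structural integrity but gives no direction and no rule for reporting change. From the formula, affected-side damage raises the index, so a rise could be read that way; no more can be said.
- **No rise in FAc is predicted.** A reader might also infer that the index is bound to move the wrong way under the trial's hypothesis. The Background proposes contralesional compensation but never says that FA in the contralesional internal capsule or peduncle will rise. The Aims section speaks of structural, functional or effective connectivity, within or between hemispheres. Low-frequency stimulation is described as inhibitory, so stimulation alone is no reason to expect higher FAc. Whether FAc moves in the 7 weeks from T0 to T2 (3 weeks of treatment plus 4 of follow-up) is unknown. All this stands.
- **DTI is one strand of several.** The mechanism question also rests on rs-fMRI and tb-fMRI, and FA AI at T0 still serves the structural-reserve aim. This stands too and limits the weight of the point.

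What the objections do not remove is the attribution problem. If FA AI changes, for whatever reason, its value alone cannot locate the change.

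**Conclusion.** The point holds as one of ambiguity. FA AI is a function of FAc/FAa alone, the contralesional side is treated in both active arms and hypothesised to compensate, and no other DTI quantity is named for the Group × Time model. A change in FA AI over T0 to T2 cannot separate contralesional gain from affected-side loss, and equal proportional changes on both sides are invisible to it.

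The algebra is exact and needs no assumed values. The illustrated size, about 0.02 on the index for a 5% change on one side, rests wholly on assumed FA values. How often the ambiguity would matter depends on whether FAc changes at all, which the protocol does not say. This is a worthwhile, inexpensive improvement to a secondary mechanistic analysis. It is not a flaw in the clinical comparison, and FA AI remains reasonable at baseline.

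**What to change.** In the Group-level analysis section:

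1. Keep FA AI, at T0 as the marker of structural reserve.
2. Name FAc and FAa as longitudinal DTI outcomes, each in the same Group × Time model. Alternatively, fit one model with Hemisphere as a further within-subject factor and report the change on each side. The Group × Time × Hemisphere term alone is again a contrast of the two sides and would not locate the change.
3. State that a change in FA AI will be interpreted only together with the changes in FAc and FAa.

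**Cost.** No new scans or ROI drawing are needed. The hemispheric means already formed for the index are pooled over all ROIs, so using those adds two outcomes and little work. Separate values for the internal capsule, peduncle and corpus callosum would have to be extracted from the ROIs already drawn and would add more outcomes. Since the section sets P < 0.05 for all analyses and mentions Bonferroni correction only for post hoc comparisons, the added outcomes should be labelled secondary or exploratory.

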### Statistical analysis

#### Sample size calculation

The sample size for this study was calculated using SPSS 21 software based on a previous study [34]. The mean score of FM-UL assessment in patients who received low-frequency rTMS treatment was 30 at baseline and increased to 43 after intervention, with a common standard deviation of 17. Furthermore, we assumed that the study would have a dropout of 30%, and thus the final target sample size was 60 participants, with 20 assigned to each group when setting a power of 80% and a significance level of 0.05.

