## Abstract

**Background:**

Previous studies have revealed that low frequency repeated transcranial magnetic stimulation (rTMS) on the contralesional primary motor cortex (cM1) is less effective in severe stroke patients with poor neural structural reserve than in patients with highly reserved descending motor pathway. This may be attributed to the fact that secondary motor cortex, especially contralesional dorsal premotor cortex (cPMd), might play an important compensatory role in the motor function recovery of severely affected upper extremity. The main purpose of this study is to compare the effectiveness of low frequency rTMS on cM1 and high frequency rTMS on cPMd in subcortical chronic stroke patients with severe hemiplegia. By longitudinal analysis of multimodal neuroimaging data, we hope to elucidate the possible mechanism of brain reorganization following different treatment regimens of rTMS therapy, and to determine the cut-off of stimulation strategy selection based on the degree of neural structural reserve.

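### The sample size rests on a before/after gain in one treated group, so the stated 80% power is unsupported for the comparison between arms

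*Protocol article*

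**What the plan says.** The Sample size calculation section of the protocol article takes its effect from one group in an earlier study, those given low-frequency rTMS. Their average FM-UL "was 30 at baseline and increased to 43 after intervention, with a common standard deviation of 17". The section then allows for 30% dropout and arrives at a total of 60, "with 20 assigned to each group when setting a power of 80% and a significance level of 0.05". It gives no figure for sham, none for high-frequency cPMd stimulation, no difference between arms, no pre-post correlation and no named test. It does not say whether 17 is the SD of scores or of change.

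The trial's question is set elsewhere. The Abstract (Background) states: "The main purpose of this study is to compare the effectiveness of low frequency rTMS on cM1 and high frequency rTMS on cPMd". Aims and hypotheses repeats this and expects cPMd-HF to be the best protocol. Group-level analysis tests it with a Group by Time mixed ANOVA over three arms, on the intention-to-treat principle, and adds that "Bonferroni correction will be employed for post hoc multiple comparisons". The number of those comparisons is not given.

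**The concern.** Power belongs to a specific contrast. The gain from 30 to 43 shows how much one treated group improved; it does not show how far two randomised arms will differ. Three features of the protocol widen that gap:

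- All three arms receive three weeks of conventional rehabilitation, so an uncontrolled gain is likely to contain improvement that every arm shares.
- The main contrast is between two active protocols. If cM1-LF gains the cited 13 points, a 13-point advantage for cPMd-HF requires that arm to gain 13 + 13 = 26.
- The Abstract says low-frequency cM1 stimulation works less well in severely affected patients with poor structural reserve, the kind of patient this trial targets. The cited gain comes from that treatment.

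What is at stake is how the result is read. If cPMd-HF and cM1-LF do not differ significantly, a reader who trusts the 80% may take this as evidence against a worthwhile difference, although the protocol never says what difference the trial could detect.

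**Working it through.** **Inputs.** From Sample size calculation: gain 43 − 30 = 13; SD 17; power 80%; alpha 0.05; dropout 30%, so 20 × 0.7 = 14 evaluable per arm; 20 randomised per arm. My assumptions: two-sided tests; three pairwise comparisons under Bonferroni, so 0.05/3 = 0.0167; T0-T1 correlations (rho) of 0.5 to 0.8; and a 6.5-point difference, half the cited gain, as an illustration.

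**Step 1: reproduce the stated number.** One-group before/after formula, normal approximation, with 17 as the SD of change:

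n = [(1.960 + 0.842) × 17/13]² = 13.42, rounded up to 14; 14/(1 − 0.30) = 20 per group, 60 in total.

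This matches. The two-sided paired t version needs 16, hence 16/0.7 = 22.9, or 23 per group, and does not match.

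**Step 2: put the same figures into a two-group comparison that ignores baseline.**

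n = 2 × (1.960 + 0.842)² × (17/13)² = 26.8, rounded up to 27 evaluable; 27/0.7 = 38.6, or 39 randomised per group.

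The t test version needs 28 evaluable (40 randomised). At alpha 0.0167 it needs 38 evaluable (55 randomised).

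**Step 3: power between two arms if the whole 13 points were the difference and the analysed SD were 17.** Two-sample t test, noncentrality (13/17) × √(n/2):

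| Evaluable per arm | alpha 0.05 | alpha 0.0167 |
|---|---|---|
| 14 | 49.5% | 31.5% |
| 20 | 65% | 47% |

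**Step 4: allow for the baseline measurement.** If 17 is the score SD at both times, the SD of change is 17 × √(2(1 − rho)): 17.0 at rho 0.5, 13.2 at 0.7 and 10.75 at 0.8. Change-score power with 14 per arm, at alpha 0.05 / 0.0167:

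| rho (assumed) | 13 points | 6.5 points |
|---|---|---|
| 0.5 | 50% / 32% | 16% / 8% |
| 0.7 | 71% / 53% | 24% / 12% |
| 0.8 | 87% / 74% | 34% / 19% |

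**Step 5: difference detectable with 80% power.** Same change-score t test, solved for the difference, in FM-UL points at alpha 0.05 / 0.0167:

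| rho (assumed) | 14 per arm | 20 per arm |
|---|---|---|
| 0.5 | 18.7 / 22.0 | 15.5 / 18.1 |
| 0.7 | 14.5 / 17.1 | 12.0 / 14.0 |
| 0.8 | 11.8 / 13.9 | 9.8 / 11.4 |

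**The case against.** The strongest reply is that the planned Group by Time analysis uses each patient's baseline, so a test that ignores it understates power. This stands. With 13 points and 14 per arm, power passes 80% at a correlation of 0.8 at alpha 0.05. Baseline adjustment by ANCOVA gives 78%/61% at 0.7 and 90%/78% at 0.8. A reader might infer from the protocol's figures that the trial simply has 50% or 32% power. The document does not support that: those values hold only for a 13-point difference, an analysed SD of 17 and 14 evaluable per arm. The 32% also needs three corrected pairs. Under intention to treat, more than 14 per arm may be analysed.

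A reader might also infer that the authors certainly ran a one-group test. That too goes beyond the text. No test is named, and the match depends on the normal approximation with 17 as the SD of change. A two-group change-score formula at a correlation of 0.75 also gives 2 × 7.85 × (17/13)² × 0.5 = 13.4, hence 14 and then 20. So the accurate statement is that no between-arm difference is stated, not that none was used.

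None of this supports the 80%. The protocol gives no correlation, and every favourable case above still treats an uncontrolled gain in one treated group as the difference between two arms. Nor is this detail that an article may leave to a fuller document: the article states its effect and its power, and the one does not support the other for the main question.

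**Conclusion.** The point holds as a mismatch between the stated effect and the comparison to be tested; no sum in the paragraph is shown to be wrong. The 80% is unsupported for cPMd-HF versus cM1-LF, and equally for either active arm versus sham.

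Its size depends on inputs the protocol does not give. If 13 points were the true difference, which is generous, power with 14 per arm runs from 50%/32% to 87%/74% (alpha 0.05 / 0.0167) as the correlation goes from 0.5 to 0.8. For half that difference it stays between 16%/8% and 34%/19%. These figures rest on two-sided t tests, an equal SD in every arm, 17 as the score SD and, for the second value in each pair, three Bonferroni-corrected comparisons.

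It would go too far to conclude that the trial must be enlarged or that its power is known to be low. What is established is that the stated power has no basis for the trial's main question.

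**What to change.** Keep 60 patients. In Sample size calculation, remove the statement that 20 per group gives 80% power, or restate it for the between-arm contrast actually tested. The restated paragraph should give:

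- the contrast;
- a justified between-arm difference;
- the SD of change, or the score SD with the pre-post correlation;
- the test and the alpha after any correction;
- the resulting power, or the detectable difference, at 14 to 20 per arm over a range of correlations.

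State also that the between-arm difference will be reported with its confidence interval, so that a non-significant result can be judged by the differences it leaves open.

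The cost is one rewritten paragraph and no extra patients. The drawback is that the stated power will probably be less favourable than 80%.
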